### Trial Design

This is a parallel-group randomized controlled pilot trial with a 1:1 allocation ratio. Participants are stratified by sex (male/female) and randomized to either (1) a control group receiving generic sleep hygiene education or (2) an experimental group receiving personalized ML-derived behavioral recommendations.

The observation period is 60 days, which aligns with PSQI requirements for 30-day data collection periods. PSQI assessments are performed at (1) baseline (prior to device use), (2) day 30 (first monitoring period), and (3) day 60 (postintervention period). This enables subjective-objective correlation while establishing a baseline (days 1‐30) to be used as a covariate for intervention analysis (days 31‐60). While 30 days may be minimal for entrenching behavior change, this pilot will establish feasibility and preliminary effect sizes for future extended trials.

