### Sample Size: Pilot Feasibility Justification

This pilot trial enrolls 32 participants (16 per arm; stratified by sex), and this is consistent with established pilot study guidelines recommending 12‐15 participants per arm for feasibility assessment [117-120]. The sample size is explicitly designed for pilot objectives, not definitive efficacy testing.

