### Pilot Objectives

The pilot objectives are as follows:

Feasibility: Can we successfully recruit, enroll, randomize, and retain participants? Can personalized ML interventions be delivered? Do participants engage with recommendations?Preliminary effect size estimation: What magnitude of difference between groups might we observe? What variability exists within groups? What baseline-to-follow-up correlation informs covariate adjustment? The estimates can inform future randomized controlled trial (RCT) sample size calculations.Methodology refinement: What challenges arise in data collection, ML model training, and intervention delivery? What proportion of nights yield usable data? Which sleep parameters show the most predictive value?Hypothesis generation: Does personalization show a promising signal warranting a larger trial? Do certain participant subgroups respond better?

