### Power Analysis Context: Not Designed for Definitive Testing

The sample size provides adequate power (>80%) only for very large effects (*d*≥1.0). For moderate effects typical in sleep research (*d*=0.3‐0.7), the power is insufficient, which is consistent with this study’s role as a feasibility-focused pilot trial. We explicitly acknowledge insufficient power for moderate effects. The power analysis table showing power for different effect sizes is presented in Multimedia Appendix 2. If moderate-to-large effects exist, we may detect a signal, and if effects are small, this pilot will yield null results, informing researchers that larger samples, longer interventions, or different approaches are needed. Both outcomes are valuable for the advancement of the field.

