### Statistical Methods

#### Primary Analysis: Single-Covariate Analysis of Covariance

The mean sleep score in the postintervention period (days 31‐60) is compared between groups using analysis of covariance with a single covariate: mean sleep score in the baseline period (days 1‐30).

$$Model:Postintervention\;score=\beta_{0}+\beta_{1}\;(group)+\beta_{2}\;(baseline\;score)+\epsilon$$

The control group is coded as “0,” and the experimental group is coded as “1.” The primary inference is based on the β₁ coefficient (group difference adjusted for baseline). The effect size is calculated as Cohen *d* with 95% CIs. Statistical significance is assessed at *α*=.05 (1-tailed per directional hypothesis), but the interpretation emphasizes the effect size magnitude and CI width, given the pilot nature of the study.

We do not use multiple covariates (age, sex beyond stratification, and behavioral factors) to avoid overfitting with the small sample size. Sex stratification in randomization addresses balance concerns without requiring covariate adjustment.

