#### Exploratory Analyses: Hypothesis Generation Only

The exploratory analyses involve the following three aspects:

Individual parameter changes: Compare the change in specific sleep variables (duration, deep sleep percentage, and REM percentage) between groups using *t* tests (unadjusted for multiple comparisons, given the exploratory nature).Adherence subgroups: In the experimental group, compare outcomes between high (≥80%) and low (<80%) self-reported adherence using the Mann-Whitney *U* test.Predictive feature patterns: Perform a descriptive analysis of which sleep parameters are most frequently identified as the top predictors across participants.

All exploratory analyses are labeled hypothesis-generating, not confirmatory. No adjustments are made for multiple comparisons, given the pilot scope of the study. Regarding the handling of missing data for the primary outcome (sleep score), participants are excluded if sufficient night data are not available in the baseline and postintervention periods, and action on the secondary outcome (PSQI) is derived from the handling of the primary outcome. This protocol contains the complete statistical analysis plan, and no separate statistical analysis plan exists.

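### The exploratory comparisons of sleep duration, deep sleep % and REM % use t tests on change; the single-covariate ANCOVA already planned for the sleep score would be modestly more precise at almost no cost

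*Protocol article*

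**What the plan says.** Under Exploratory Analyses: Hypothesis Generation Only, the Protocol article states that it will "Compare the change in specific sleep variables (duration, deep sleep percentage, and REM percentage) between groups", using t tests. No baseline covariate is named. The word unadjusted in that item refers to multiple comparisons, not to baseline.

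The primary outcome is handled differently. Primary Analysis: Single-Covariate Analysis of Covariance compares the days 31-60 mean sleep score between arms by "analysis of covariance with a single covariate: mean sleep score in the baseline period". The argument there about overfitting is directed at using several covariates; it does not speak against a single baseline term.

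The three parameters come from the same watch and the same nights as the sleep score, either recorded directly (duration) or derived from the recorded stages (deep % and REM %), as Tables 1 and 2 show. Each therefore has its own days 1-30 mean.

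The exploratory section also says that the article contains the complete analysis plan and that no separate one exists, so the t test on change is the final specification. Interpretation Guidance promises effect sizes and CIs. Pilot Objectives includes the question "What baseline-to-follow-up correlation informs covariate adjustment" among the quantities that could inform a later trial.

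**The concern.** A t test on change subtracts the baseline in full, which fixes its coefficient at 1. ANCOVA estimates that coefficient from the data. When the two periods are imperfectly correlated and have similar spread, the best coefficient is below 1. Full subtraction then adds noise, and it also leaves part of any chance baseline difference between arms in the estimate.

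At 16 per arm such differences are not small, and stratifying by sex does not balance baseline sleep duration or stage percentages. In a pilot whose output is effect sizes and interval widths, what is at stake is some avoidable width in the parameter-level CIs. The article gives no reason for using a different method from the one it uses for the sleep score.

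**Working it through.** **Inputs.** From the article: a "parallel-group randomized controlled pilot trial with a 1:1 allocation ratio" with 32 participants, 16 per arm (Trial Design; Sample Size). Alpha is 0.05, "1-tailed per directional hypothesis", stated for the primary analysis only; none is stated for the exploratory t tests. Assumptions made here: rho is not given, so a range is shown; variances are equal in both periods and both arms; 95% CIs and power are two-sided at 0.05.

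**The plan's own power figure first.** The article says "The sample size provides adequate power (>80%) only for very large effects", meaning d of 1.0 or more. For two groups of 16 and d = 1.0, the t test gives 86.8% one-sided and 78.1% two-sided; the normal approximation gives 88.2% and 80.7%. The statement reproduces with the plan's one-sided alpha.

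**Variances.** In units of the squared between-participant SD:

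- change score: 2(1 - rho), with 30 df;
- ANCOVA: (1 - rho²), with 29 df, multiplied by (N - 3)/(N - 4) = 29/28 because the slope must be estimated.

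Leaving out the 29/28 factor, the ratio of change to ANCOVA variance is 2/(1 + rho). That is 1.54 at rho 0.3, 1.33 at 0.5, 1.18 at 0.7, 1.11 at 0.8 and 1.05 at 0.9.

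**Width of the 95% CI, with the penalty.** The ratio is sqrt[2(1 - rho)] × t(0.975, 30) divided by sqrt[(1 - rho²) × 29/28] × t(0.975, 29), where the t quantiles are 2.0423 and 2.0452. At rho 0.5 this is (1.000 × 2.0423)/(0.8814 × 2.0452) = 1.133.

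| rho | change-score CI wider than ANCOVA by |
|---|---|
| 0.3 | 22% |
| 0.5 | 13% |
| 0.7 | 6% |
| 0.8 | 3% |
| 0.9 | 1% |

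A simulation with normal data (8,000 runs per value) gave ratios of 1.13, 1.06, 1.03 and 1.01 at rho 0.5, 0.7, 0.8 and 0.9.

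**Break-even.** Setting the two widths equal gives rho = 2 × (28/29) × (2.0423/2.0452)² - 1, which is about 0.93. Above that, ANCOVA is very slightly the wider: at rho 0.95 the ratio is 0.994.

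**Power.** Noncentral t, two-sided 0.05, with d in raw SD units, taking values from the article's power section:

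| rho | d | change | ANCOVA |
|---|---|---|---|
| 0.5 | 0.5 | 28% | 34% |
| 0.5 | 0.7 | 48% | 58% |
| 0.5 | 1.0 | 78% | 87% |
| 0.7 | 0.5 | 42% | 47% |
| 0.7 | 0.7 | 70% | 75% |
| 0.7 | 1.0 | 94% | 96% |

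At rho 0.9 and d = 0.5 the two are 86.4% and 86.9%.

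**Chance imbalance.** The standard error of a baseline difference between arms is sqrt(2/16) = 0.35 SD. A change score carries (1 - rho) of the observed difference into the estimate. For a one-standard-error imbalance that is 0.5 × 0.35 = 0.18 SD at rho 0.5 and 0.3 × 0.35 = 0.11 SD at rho 0.7.

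**The case against.** The strongest defence is that nothing here is wrong. A between-arm t test on change is a valid comparison under randomization, the analyses are labelled hypothesis-generating, no decision depends on them, and ANCOVA is not promised for these parameters. All of that stands, and it limits the point to efficiency. The exploratory label explains the absence of a multiplicity correction; it is not a reason to prefer the less precise estimator.

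A second objection is that the gain may be very small. Each parameter is a mean over up to 30 nights, and averaging removes night-to-night noise, so rho could well be high. At 0.9 the gain is negligible. This also stands. But rho is unknown, and ANCOVA gives up almost nothing if it proves high.

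The equal-variance assumption is open to question too: ML-Derived Heterogeneity by Design expects that the experimental arm may be more variable. The percentages are therefore a guide.

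Three stronger readings are tempting but unsupported:

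- A reader might infer that the change-score estimates are biased. They are not, on average over randomizations; the distortion is conditional on the imbalance that happens to arise.
- A reader might infer that the plan fails its own objective because the t tests return no baseline coefficient for each parameter. Pilot Objectives asks for a correlation to inform planning, not a coefficient for every parameter. The primary ANCOVA data supply it for the sleep score, and a t test does not prevent anyone from reporting it for the rest.
- A reader might infer that power falls short of a stated target. The article's power statement concerns the trial's sample size, and it already concedes that power is insufficient for effects it calls moderate ("For moderate effects typical in sleep research", d = 0.3 to 0.7). It claims no power for these three parameters.

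Finally, the secondary PSQI analysis also uses a t test on change, where the same reasoning carries more weight because that outcome ranks higher.

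**Conclusion.** The point holds as a modest gain in precision that the plan leaves unused, not as an error or a contradiction. For any rho below about 0.93, ANCOVA on the parameter's own baseline gives narrower expected intervals at this sample size. The benefit is material if rho is around 0.3 to 0.5, small at 0.7 to 0.8 and negligible from 0.9 upwards. ANCOVA also removes the conditional effect of chance baseline imbalance.

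The direction does not depend on the choice of alpha; the power figures do, and they rest on an assumed two-sided 0.05. All the sizes rest on equal variances and on values of rho that the article does not supply. The conclusions of the trial would not change, and the priority is low.

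**What to change.** In the item on individual parameter changes under Exploratory Analyses, replace the t tests on change with the primary model applied to each parameter: the participant's days 31-60 mean regressed on group and on the same parameter's days 1-30 mean. For duration, deep % and REM %, report the adjusted difference with its 95% CI, the residual SD and the baseline-to-follow-up correlation. The last two are directly usable for planning a later ANCOVA-based trial. Keep the exploratory label and the statement that multiplicity is not adjusted for.

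The cost is one degree of freedom per model, the 29/28 variance penalty and a change of wording. No new data are needed, and the code is that of the primary analysis. The change should be made before outcomes are analysed, and the PSQI comparison could be considered in the same edit.

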### Interventions

#### Control Intervention: Generic Sleep Hygiene Education

Control group participants receive standardized sleep hygiene education on day 30, covering general recommendations applicable to all adults. Examples include maintaining a consistent sleep-wake schedule and sleeping between 7 and 9 hours per night. These recommendations are not personalized to individual sleep patterns.

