### Personalized Sleep Intervention Framework

The intervention content is based on individual ML feature importance ranking, and participants receive nonpharmacological recommendations from a predefined library (Multimedia Appendix 1) targeting their top 2‐4 predictive sleep parameters [108-116]. Example recommendations for TST optimization (if sleep_duration is a key predictor) are as follows: ensure wake-up time commitment for too much sleep and bedtime commitment for too little sleep. Example recommendations for sleep efficiency enhancement (if movement_awakening is a predictor) are as follows: use white noise, ensure a quiet environment, and restrict caffeine intake (avoid intake ≤6 hours before bedtime). Example recommendations for sleep timing regulation (if sleep_cycle is a predictor) are as follows: ensure a consistent sleep-wake schedule and keep the bedroom cool (around 18 °C‐20 °C).

Experimental group participants receive personalized recommendations, and the top 2‐4 recommendations are explained by the researcher during the in-person meeting. Adherence tracking involves self-reported compliance assessed at study closure (0%‐100% scale). Control group participants receive generic sleep hygiene education without personalization by the researcher during the in-person meeting.

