### Exploratory Outcomes

The exploratory outcomes include (1) individual sleep parameter changes (which specific variables improve), (2) adherence to personalized recommendations (self-reported 0%‐100% scale), and (3) behavioral confounders (alcohol consumption, exercise, and stress documented in the closure interview).

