### Data Collection Quality Control

The following measures are implemented for user-related issues: (1) noncompliance: participants with missing data for >20% of nights are excluded and replaced; (2) charging issues: backup chargers are provided, and daily battery monitoring is required; (3) unauthorized modifications: settings are locked, and violations lead to replacement; and (4) sync delays: daily commitment for cloud backup within 24 hours. The following measures are implemented for device-related issues: (1) fragmented recording: nights without combined scores are excluded; (2) data mismatch: nights with artifact conflicts are excluded; and (3) sync errors: multiple attempts are made with escalating intervals. For sensor inaccuracies, quality control is performed through sleep diaries, and outliers trigger replacement. Excluded participants are replaced from the recruitment pool to maintain the sample size. The expected night exclusion impact is around 18%, with anticipated replacement ensuring the target sample.

Subjective data collection is performed through PSQI forms completed on paper. Information is manually entered by the researcher into a password-protected spreadsheet with self-verification (data are entered twice by the researcher to ensure accuracy). Data are processed through the manufacturer’s algorithms to interpret the findings of the 10 explanatory variables and the target variable (Table 1).

**Table 1. T1:** Target and explanatory variables collected by the wearable (indispensable for this study).

Variable		Description	Unit	Data type
Explanatory variable				
sleep_duration		Sum of N1, N2, N3, and REM^a^	Minutes	Integer
movement_awakening		Count of movement during sleep	Number	Integer
sleep_cycle		Count of sleep cycles	Number	Integer
mental_recovery		Score assigned according to the REM phase	Score (0‐100 scale)	Integer
physical_recovery		Score assigned according to the N3 phase	Score (0‐100 scale)	Integer
efficiency		real_total_sleep by sleep_duration	Percentage	Integer
Transition_N1		Sum of minutes of sleep in the N1 phase	Minutes	Integer
Light_N2		Sum of minutes of sleep in the N2 phase	Minutes	Integer
Deep_N3		Sum of minutes of sleep in the N3 phase	Minutes	Integer
REM		Sum of minutes of sleep in the REM phase	Minutes	Integer
Target variable				
sleep_score		Score assigned for the night	Score (1‐100 scale)	Integer

a REM: rapid eye movement.

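### The exploratory comparison omits two parameters that the example advice targets, and its deep and REM percentages can move with sleep length alone

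*Protocol article*

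**What the plan says.** The Exploratory Outcomes section lists "individual sleep parameter changes (which specific variables improve" as its first item, without limiting which variables are meant. The section Exploratory Analyses: Hypothesis Generation Only turns this into an instruction to "Compare the change in specific sleep variables (duration, deep sleep percentage, and REM percentage) between groups" by unadjusted t tests. The same section says that the article holds the whole analysis plan and that no further plan exists, so the list cannot be assumed to be completed elsewhere.

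The Personalized Sleep Intervention Framework gives three worked examples of advice, each tied to a watch variable:

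- sleep_duration: "ensure wake-up time commitment for too much sleep and bedtime commitment for too little sleep"
- movement_awakening: "Example recommendations for sleep efficiency enhancement (if movement_awakening is a predictor) are as follows"
- sleep_cycle: advice on sleep timing regulation

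Controls also get advice that bears on sleep length. Their education includes "maintaining a consistent sleep-wake schedule and sleeping between 7 and 9 hours per night" (Control Intervention: Generic Sleep Hygiene Education).

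Table 1 (Data Collection Quality Control) shows that the watch records movement_awakening and sleep_cycle, and also the stage times in minutes. Deep_N3, for example, is the "Sum of minutes of sleep in the N3 phase". Table 2 (Results) defines Deep_pct and REM_pct as percentages of sleep. It does not say whether the denominator is sleep_duration or real_total_sleep, which excludes N1.

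**The concern.** Two things do not fit together.

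1. **Coverage.** The outcome asks which variables improve, but the planned comparison omits two variables that the article itself names as targets of advice. For participants whose advice concerns movement or sleep cycles, the plan has no group comparison of the parameter they were asked to change.

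2. **Scale.** Deep and REM percentages are shares of a total that some of the advice is meant to change. If sleep lengthens and the added time holds proportionally less deep sleep, the deep percentage falls although no deep sleep is lost. If sleep shortens, it can rise with no gain. A difference between arms in sleep length can then be read as a difference in sleep architecture.

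What is at stake is the reading of the parameter-level results, which the article intends to use to generate hypotheses for later work.

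**Working it through.** The plan gives no figure of its own on this point, so there is none to reproduce.

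**Step 1. Coverage.** Variables in the example recommendations: sleep_duration, movement_awakening, sleep_cycle. Variables in the planned comparison: duration, deep percentage, REM percentage. The overlap is sleep_duration only, so 2 of the 3 example targets have no planned comparison. Both are among the 18 variables of the final dataset (Table 2).

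**Step 2. How a percentage moves with its denominator.** New percentage = 100 × (deep minutes + added deep minutes) / (total sleep + added sleep). The starting values are assumed, because the article gives none.

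| Case | Calculation | Change (points) |
|---|---|---|
| 360 to 420 min, deep fixed at 60 min | 60/360 = 16.7%; 60/420 = 14.3% | −2.4 |
| Same, 5% of the added hour is deep | 63/420 = 15.0% | −1.7 |
| Same, 10% of the added hour is deep | 66/420 = 15.7% | −1.0 |
| 600 to 540 min, deep fixed at 60 min | 60/600 = 10.0%; 60/540 = 11.1% | +1.1 |

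In the second and third rows deep minutes rise while the percentage falls. Over assumed baselines of 360 to 420 min and deep shares of 10 to 20%, with deep minutes fixed:

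- 15 min added: −0.34 to −0.80 points
- 30 min added: −0.67 to −1.54 points
- 60 min added: −1.25 to −2.86 points
- 30 min removed: +0.77 to +1.82 points

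**Step 3. From one sleeper to a group contrast.** The contrast shifts only by the difference in net duration change between arms. Suppose that one arm gains 30 min more than the other, from 390 min with 15% deep (58.5 min). Then 58.5/420 = 13.93%, a shift of −1.07 points. Dividing by an assumed SD of change, with 16 per arm and a two-sided t test at .05 (the article does not state the sidedness of these tests):

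| SD of change (points) | Standardized shift | Chance of p < .05 from the shift alone |
|---|---|---|
| 1.5 | 0.71 | 0.50 |
| 2 | 0.54 | 0.31 |
| 3 | 0.36 | 0.17 |
| 4 | 0.27 | 0.11 |

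With a net difference of 15 min the shift is 58.5/405 − 15% = −0.56 points, that is 0.37 to 0.14 SD, and the chance is 0.17 to 0.07. With no net difference in duration change, this mechanism produces essentially no shift.

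**Step 4. Minutes have the mirror problem.** At an unchanged stage mix of 16.7%, going from 360 to 420 min raises deep sleep from 60 to 70 min. Minutes then show a gain although the composition is the same. Percentages describe composition and minutes describe amount; neither is sufficient alone when the total moves.

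**Step 5. Price of more tests.** For independent tests at .05, the chance of at least one false positive is 1 − 0.95³ = 14% with three, 1 − 0.95⁵ = 23% with five, and 1 − 0.95⁷ = 30% if the two minutes rows are tested as well. The variables are correlated, so these figures are approximate.

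**The case against.** The case for leaving the list alone is substantial.

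- **The examples are only examples.** They come from a library in Multimedia Appendix 1, which was not available for this review. The section ML-Derived Heterogeneity by Design also names REM, deep sleep, sleep timing and wake episodes as possible targets. Deep sleep and REM are in the planned list. This stands: the gap concerns movement_awakening and sleep_cycle, not targeted parameters in general.
- **Gains elsewhere are not invisible.** A reader might infer that effective advice on awakenings or cycles could not show up at all. The documents do not support that. The primary outcome section describes the sleep score as combining duration, architecture, efficiency and fragmentation. A descriptive look at recommendation types is planned, and the variables stay in the dataset.
- **The arm-level shift is diluted.** Duration advice goes only to participants for whom sleep_duration is a key predictor, it works in both directions, and controls are also advised on sleep length. As an illustration, suppose one third of the experimental arm gains 60 min, nobody shortens and controls do not change. The −1.0 to −2.4 points of Step 2 become −0.3 to −0.8, or about −0.1 to −0.3 SD for an SD of 3 to 4 points.
- **Duration is in the same list**, so a careful reader can see the denominator move.
- **The analyses are labeled hypothesis-generating**, and Interpretation Guidance stresses effect sizes and intervals.

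These points limit the weight of the concern. They do not close the gap between an open question about which variables improve and a list of three, and they do not tell the reader of a percentage whether the stage minutes changed.

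**Conclusion.** The point holds as a modest one about coverage and presentation. The list omits two parameters that the article names as targets of advice and records every night, and it reports architecture only as shares of a total that the advice may change. The coverage gap rests on the text alone. The denominator effect is arithmetic: its direction is fixed whenever stage minutes change less than proportionally with total sleep. Its size in this trial is unknown, because it depends on the net difference in duration change between arms and on baselines and SDs that the article does not give. It could be negligible, and it could run either way.

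Two stronger conclusions are tempting and unsupported. One is that percentages are the wrong measure and should be dropped; Step 4 shows that minutes alone mislead in the opposite way. The other is that the pilot will carry the wrong parameters into the next trial. The article bases the future sample size on pilot effect sizes and variability, and it assigns the exploration of responsive parameters to the dataset as a whole, not to these three tests.

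The primary and secondary analyses are unaffected. The priority is low to moderate.

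**What to change.** In Exploratory Analyses: Hypothesis Generation Only:

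1. Add movement_awakening and sleep_cycle to the between-group comparisons of change.
2. Report the change in Deep_N3 and REM minutes beside, not instead of, the two percentages.
3. State the denominator of Deep_pct and REM_pct (sleep_duration or real_total_sleep).
4. Say that percentages and minutes will be read together with the change in duration.
5. Give every row as an effect size with its CI, so that a longer list does not become a search for small p values.

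No new data, visits or participants are needed, because all these variables are already collected. The cost is a somewhat longer exploratory table and the higher chance of an isolated false positive shown in Step 5, which is acceptable if the rows are reported as estimates and kept labeled exploratory.

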### Adherence Assessment

In the experimental group, adherence to personalized recommendations is assessed through self-report at the day 60 closure interview. Participants rate adherence on a scale from 0% to 100% for each recommendation provided. In the control group, adherence to generic sleep hygiene is assessed in a similar manner. Device wear adherence is monitored through objective data. Participants with missing data for >20% of nights may be excluded and replaced.

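### The exploratory adherence comparison leaves out the baseline sleep score and does not name its outcome, so it is biased, in a direction that depends on the reading, whenever adherence is related to prior sleep

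*Protocol article*

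**What the plan says.** Under Exploratory Analyses the protocol says: "In the experimental group, compare outcomes between high (≥80%) and low (<80%) self-reported adherence", by the Mann-Whitney U test. It names no covariate. It does not say whether the outcome is the postintervention sleep score, its change from baseline, or the PSQI.

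Under Adherence Assessment, "adherence to personalized recommendations is assessed through self-report at the day 60 closure interview", which is after the whole outcome period of days 31-60. The rating is made per item: "Participants rate adherence on a scale from 0% to 100% for each recommendation provided". No rule is shown for combining several ratings into one value before the 80% cut. For the other arm, "In the control group, adherence to generic sleep hygiene is assessed in a similar manner", but no listed analysis uses those data.

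The primary analysis is an analysis of covariance "with a single covariate: mean sleep score in the baseline period (days 1‐30"), so the baseline score is collected and already in use. On size, "This pilot trial enrolls 32 participants (16 per arm; stratified by sex"), so the adherence comparison has at most 16 people before it is split.

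The same section labels all exploratory analyses as hypothesis-generating and states that no separate analysis plan exists, so this item will not be specified further elsewhere.

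**The concern.** The natural question for this analysis is whether people who follow the personalised advice sleep better because they follow it. The test asks something else: whether the outcome distribution differs between people who report high adherence and people who report low adherence. The two questions coincide only if adherence is unrelated to everything else that drives the outcome.

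The most obvious such driver is the person's own earlier sleep score. The protocol's example recommendations include a regular sleep-wake schedule and a quiet bedroom, so someone who already does these things could report high adherence without changing anything. The randomised comparison is adjusted for baseline. This non-randomised comparison, which needs the adjustment more, is not.

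What is at stake is interpretation. The pilot objectives ask whether personalisation shows a signal that would justify a larger trial, and a gradient with adherence could be read as one. The protocol also undertakes to report effect sizes, and this one would be biased whether or not the test rejects.

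**Working it through.** The plan gives no figure for this comparison, so there is none to reproduce. Its only power statement concerns the comparison between arms.

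**Inputs from the protocol.** There are 16 participants in the experimental arm, a cut at 80% and a Mann-Whitney test. The sidedness of this test is not stated. The primary test is one-tailed at .05.

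**Assumptions, because the protocol gives no values.**
- Baseline-to-follow-up correlation of the mean sleep score, *r_bp*: 0.5, 0.7, 0.8. Estimating it is one of the pilot's objectives.
- Correlation of adherence with baseline score, *r_ab*: 0, 0.3, 0.5.
- High/low split: 8/8, with 5/11 as a variation.
- Adherence has no effect: given baseline, the postintervention score is independent of adherence. Scores are standard normal, with equal SD in both periods.

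**Size of the bias.** With 16 people split 8/8 on a normal adherence variable, the top and bottom halves differ in mean adherence by *D* = 1.52 SD. The expected normal scores of the upper eight are 1.766, 1.285, 0.990, 0.763, 0.570, 0.396, 0.234 and 0.077. They sum to 6.081, their mean is 0.760, and twice that is 1.52. Then:

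- gap in postintervention score = *r_ab* × *r_bp* × *D*
- gap in change score = *r_ab* × (*r_bp* − 1) × *D*
- gap after adjustment for baseline = 0

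| *r_ab* | *r_bp* | Gap, post score (SD) | Gap, change (SD) |
|---|---|---|---|
| 0.3 | 0.5 | 0.3 × 0.5 × 1.52 = 0.23 | 0.3 × (−0.5) × 1.52 = −0.23 |
| 0.3 | 0.8 | 0.3 × 0.8 × 1.52 = 0.36 | 0.3 × (−0.2) × 1.52 = −0.09 |
| 0.5 | 0.5 | 0.5 × 0.5 × 1.52 = 0.38 | 0.5 × (−0.5) × 1.52 = −0.38 |
| 0.5 | 0.8 | 0.5 × 0.8 × 1.52 = 0.61 | 0.5 × (−0.2) × 1.52 = −0.15 |

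A positive gap favours high adherers.

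**False rejection.** Simulation with 20,000 data sets per cell, exact Mann-Whitney on the postintervention score, 8/8 split, two-sided .05:

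| *r_ab* | *r_bp* 0.5 | *r_bp* 0.7 | *r_bp* 0.8 |
|---|---|---|---|
| 0 | about 5% | about 5% | about 5% |
| 0.3 | 7.1% | 9.1% | 10.3% |
| 0.5 | 10.8% | 16.9% | 21.2% |

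- One-sided at .05, the ranges are 9.3-14.8% at *r_ab* = 0.3 and 15.9-28.8% at 0.5.
- With a 5/11 split (two-sided), they fall to about 5-8% and 8-17%.
- If the outcome is change, one-sided rejection in favour of high adherers falls to 1.6-2.3% at *r_ab* = 0.3 (8/8).
- A linear model that adds the baseline score rejects in about 5% in every cell.

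**What baseline adjustment does not cure.** Suppose the day 60 self-rating also follows how the person slept in days 31-60. With a loading of 0.3 or 0.5 on the follow-up residual (*r_bp* = 0.7, 8/8 split, still no adherence effect), the baseline-adjusted model rejects in 13-14% and 31-33% respectively.

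**The case against.** The strongest reply is that nothing in the protocol links adherence to baseline sleep, and even the sign is open: worse sleepers may be the more motivated. This stands. A reader might infer that the test will reject because better sleepers adhere more, or that an inert intervention would as a rule produce an adherence gradient. The documents support neither. At zero correlation the test holds its level, and even at an assumed 0.5 it usually does not reject.

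The undefined outcome can also be read the other way. The neighbouring PSQI and sleep-parameter analyses use change. On that reading the same mechanism makes high adherers look worse. This stands against any claim that the plan favours personalisation. It does not rescue the analysis, because the sign of the bias then turns on an undefined word.

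The protocol also confines this analysis to hypothesis generation and claims no dose-response. That lowers the severity but does not remove bias from a reported estimate.

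It is tempting to ask for a model over both arms with a group-by-adherence interaction. That would cancel a reporting bias that is equal in the two arms. However, it would be zero if following advice helped equally in both. It would detect an effect of 0.3 SD present only in the experimental arm in about 16-25% of trials with 32 people. It would also put adherence to two different kinds of advice on one scale. The protocol avoids extra covariates because of the small sample. The interaction is a debatable choice, not a needed correction. One baseline covariate is what the primary model already carries.

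**Conclusion.** The concern holds in conditional form. As written, the comparison cannot separate following the advice from having slept better or worse beforehand, and the direction of the error depends on which outcome is meant. Under assumed adherence-baseline correlations of 0.3-0.5 and baseline-to-follow-up correlations of 0.5-0.8, an even split gives a false rejection rate of about 7-21% (two-sided .05) on the postintervention score, where 5% is intended, and a spurious gap of about 0.2-0.6 SD. With adherence unrelated to baseline there is no excess. The range rests wholly on those assumptions, since the protocol gives neither correlation. Severity is minor: the analysis is exploratory, and the primary analysis of covariance is untouched.

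**What to change.** In the adherence item of the exploratory analyses:

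1. Name the outcome as the mean sleep score over days 31-60.
2. State how the per-recommendation ratings are combined into one adherence value per participant.
3. Replace the Mann-Whitney test with a linear model, within the experimental arm, of that outcome on adherence and the mean baseline sleep score. Report the adherence estimate with its 95% CI.
4. Describe the result as a non-randomised association. State that adherence is self-rated at day 60, after the outcome period, and that baseline adjustment does not remove bias from that source.
5. Optionally, show the same baseline-adjusted estimate for the control arm alongside, descriptively and without a test between arms.

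The cost is a change of text. The baseline scores and the adherence ratings in both arms are already collected. The model leaves 16 − 3 = 13 residual degrees of freedom, so the interval will be wide, and the rank test's freedom from distributional assumptions is given up.
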